
**Figure 1 figure1:**
[figure not shown]
Consolidated Standards of Reporting Trials (CONSORT) flow diagram.

Inclusion and exclusion criteria.Inclusion criteriaParticipants irrespective of gender, religion, and socioeconomic status.Participants affected with gadget addiction as per case definition, that is internet addiction test score: 31-79.Age group between 6-16 years with signs and symptoms of gadget addictions as per *ICD-10* (*International Statistical Classification of Diseases, Tenth Revision*) or 11 as follows.Parents who are willing to provide written informed consent for their children to be included in the study.Exclusion criteriaInternet addiction test score >80.Children aged <6 years and those aged >16 years.Parents who are not willing to provide written informed consent for their children to be included in the study.Children experiencing from behavioral diseases, locomotor diseases, genetic diseases, and systemic disorders.

**Table 1 table1:** Overview of interventions.

	Group P	Group N	Group C
Participants, n	80	80	External group
Name of medication	Medhya Rasayana	Nonpharmacological	Cognitive behavioral therapy
Dosage form	Young’s formula	As per schedule	—^a^
Duration	90 days	90 days	—
Assessment with IAT^b^ scale	0, 30, 60, and 90 days	0, 30, 60, and 90 days	—
Follow up with the IAT scale, digital addiction scale, and *DSM-5*^c^ scale	180th day	180th day	—
Route or mode of administration	Oral	—	—
Anupana	Lukewarm water	—	—

^a^Not applicable.

^b^IAT: internet addiction test.

^c^*DSM-5*: *Diagnostic and Statistical Manual of Mental Disorders* (Fifth Edition).

**Table 2 table2:** Overview of Ayurveda nonpharmacological intervention.

Intervention	Details of method	Duration and frequency
Counseling (Satvavajaya)	Counseling about hazardous effects of mobile and benefits of mobile deaddiction	Fortnight 1 session with parents and child separately
Yoga therapy	Surya Namaskar, Dhyana	Daily
Encouragement for indoor and outdoor games	Patients will be counseled to play indoor and outdoor games daily	Daily for1hour
Encouragement towards attending social programs	Parents will be guided for engagement of children in learning new things, in group activities with peers, etiquette	“Si-opus sit” Whenever required and feasible
Encouragement of parent-child relationship	Parents are advised to spend time with their children. And advised to give a reward for not using mobile to child.	Minimum 2 hours of quality time daily by parents
Targeted reduction in Gadget use time	Reduced time will be used for adventure, bravery cognitive skill-oriented things, sports, and yoga.	By Padanshik karma reduces gadget use time by one-fourth part each week

### Participants

The required sample size was calculated by using the following formula.

To evaluate the effectiveness of the therapeutic modalities for managing internet addiction, several key parameters are defined. The type I error rate () is set at 5% and the type II error rate (β) is set at 20%. The true proportion difference, represented by ε, is assumed to be 0. δ denotes the clinically relevant difference at 20% superiority. Initially, the proportion of individuals with internet addiction (P1) is 62.22% (0.622). After the intervention (P2), this proportion decreased to 36.2% (0.362). To determine the appropriate sample size for the study, a clinically accepted difference of 20% is used. The sample size is calculated according to the formula N=(1.64+0.84)2(0.622)(1–0.622) +0.362(1–0.362)/(0.20)2. Based on this formula, the required sample size is 72 individuals per group. To account for a 10% dropout rate, the sample size is increased to 80 per group.

Therefore, 80 participants will be recruited after randomization in each group from the Kaumarbhritya OPD of Mahatma Gandhi Ayurved College Hospital and specialty camps held in peripheral villages of Wardha city. A computer-generated random number table will be used to avoid selection bias in the study. The principal investigator will carry out the process of randomization and enroll the participants. To be eligible for participation, participants should fulfill the inclusion criteria as mentioned in Textbox 2. Patients having any characteristics of exclusion criteria will be excluded from participation in the study.

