#### Statistical Analysis

The data collection phase will be concluded with statistical analysis. Repeated measures ANOVA test, and chi-square test, will be used for statistical interpretation. A statistician consultation will be considered for the selection of the proper statistical method.

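### The 72 per group reproduces, but a true difference of 0, before/after rates and an undeclared one-sided z leave the 80% power unattached to any comparison the protocol states

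*Protocol article*

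**What the plan says.** All the inputs stand in one paragraph of the Protocol article, Methods, Participants.

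- Error rates: type I 5%, and "the type II error rate (β) is set at 20" percent. The text does not say whether the 5% is one-sided or two-sided.
- Difference and margin: "The true proportion difference, represented by ε, is assumed to be 0. δ denotes the clinically relevant difference at 20% superiority".
- Rates: "Initially, the proportion of individuals with internet addiction (P1) is 62.22% (0.622"); the second rate, P2 = 0.362, is the proportion after the intervention.
- Formula, with brackets and exponents lost in the text: "N=(1.64+0.84)2(0.622)(1–0.622) +0.362(1–0.362)/(0.20)2".
- Result: 72 per group, raised to 80 for 10% dropout.

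Elsewhere, Study Design calls the trial a three-arm superiority trial in which only two groups, P and N, are randomized (1:1). The third, cognitive behavioral therapy (CBT), is published data from outside the trial. The alternative hypothesis is that at least one Ayurveda intervention is more effective than the control group, and the text below it speaks of whether the three interventions differ. Statistical Analysis states: "Repeated measures ANOVA test, and chi-square test, will be used for statistical interpretation".

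**The concern.** A superiority trial needs an assumed nonzero difference between its arms. Here that difference is set to 0, the two rates describe change over time rather than a contrast between arms, their gap is not the figure in the denominator, and the z value implies a one-sided test that is nowhere declared. Each is a question about what the calculation refers to, and together they leave the reader unable to say what the 80% is the power for.

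This paragraph is the only justification given for randomizing 160 children. If P and N do not differ significantly at the end, the reader will want to know what size of difference the trial could have detected. As written, the protocol cannot answer that.

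**Working it through.** **Inputs (Participants section).** z values 1.64 and 0.84; P1 = 0.622; P2 = 0.362; ε = 0; δ = 0.20; dropout 10%.

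**1. The plan's own figure.** With brackets and exponents restored:

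- V = 0.622 × 0.378 + 0.362 × 0.638 = 0.46607
- n = (1.64 + 0.84)² × V / 0.20² = 6.1504 × 0.46607 / 0.04 = 71.66, rounded up to 72
- 72 / 0.9 = 80

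Both stated figures reproduce.

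**2. What ε = 0 does.** I assume the usual margin formula, whose denominator is (ε − δ)². With ε = 0 and δ = 0.20 it becomes 0.20² whatever the sign of the margin, so 72 appears whether the aim is to rule out a 20-point deficit or to show a 20-point advantage. The power is not the same. With SE = √(0.46607 / 72) = 0.0805 and one-sided 5%:

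- Non-inferiority, margin 0.20, true difference 0: Φ(0.20/0.0805 − 1.645) = 80%
- Simple superiority, true difference 0: 5%, the type I error rate
- Superiority by more than 0.20, true difference 0: Φ(−0.20/0.0805 − 1.645) = 0.002%

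Only the first gives 80%, and the protocol does not claim non-inferiority.

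**3. Three different differences.** The paragraph holds ε = 0, P1 − P2 = 0.622 − 0.362 = 0.26, and 0.20 in the denominator. They cannot all be the true difference of one comparison.

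**4. Power at 72 per group under the other readings**, from Φ((d − margin)/SE − z), with z = 1.645 one-sided or 1.96 two-sided:

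| Reading | One-sided 5% | Two-sided 5% |
|---|---|---|
| True difference 0.20, no margin | 80% | 70% |
| True difference 0.26, no margin (0.622 and 0.362 taken as arm rates) | 94% | 90% |
| True difference 0.26, superiority margin 0.20 | 18% | 11% |

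If all 80 per group are analysed, SE = √(0.46607 / 80) = 0.0763, and two-sided power for 0.20 is Φ(0.20/0.0763 − 1.96) = 75%.

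**5. Sensitivity to the arm rates.** The variance in step 1 comes from the before/after rates. Two illustrative pairs 20 points apart, both containing the plan's 36.2%, at 72 per group and two-sided 5%:

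- 56.2% vs 36.2%: V = 0.562 × 0.438 + 0.362 × 0.638 = 0.4771; SE = 0.0814; power = Φ(2.457 − 1.96) = 69%
- 36.2% vs 16.2%: V = 0.362 × 0.638 + 0.162 × 0.838 = 0.3667; SE = 0.0714; power = Φ(2.802 − 1.96) = 80%

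**6. Size for 80% power, two-sided, with the plan's variance.** (1.96 + 0.84)² × 0.46607 / 0.04 = 91.35, so 92 per group; 92 / 0.9 = 102.2, so 103 with dropout.

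**The case against.** The strongest reply is that nothing in the arithmetic fails and the number of children may well be adequate. That stands. A reader might infer that 72 per group falls short of 80% power. The documents do not support this as a flat statement: 72 gives 80% for a one-sided 5% test of a real 20-point difference, about 80% two-sided for 36.2% vs 16.2%, and about 90% two-sided if 0.622 and 0.362 are taken as the arm rates.

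A reader might also call the 1.64 an error. It is not one in itself. The alternative hypothesis is directional, Statistical Analysis gives no sidedness and leaves the choice of method open to a statistician, and a chi-square test on a 2 × 2 table can be run directionally. What remains is that the choice is undeclared and does not match the named tests as they are ordinarily run, which is two-sided. The 70% figure depends on that two-sided reading.

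The third tempting inference starts from the entry criterion, "Participants affected with gadget addiction as per case definition, that is internet addiction test score: 31-79": every enrolled child is addicted, so the initial rate must be 100% and not 62.2%. That assumes the 62.2% was measured against the same threshold, and the sample size paragraph gives neither a threshold nor a source for it. The narrower point stands: the two rates are labelled before and after, so they are not rates in groups P and N.

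An unseen analysis plan might settle the sidedness. It would not make a true difference of 0 consistent with a superiority aim, since that assumption is in the protocol's own text.

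**Conclusion.** The point holds as a contradiction among stated assumptions, not as an arithmetic error or a demonstrated shortfall in numbers. The 72 and 80 are computed correctly. The 80% power is not established for any comparison the protocol states, because each reading that yields 80% or more sets aside something in the text: the zero difference, the superiority aim, or the description of the rates as before and after.

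At 72 per group with the plan's variance, power for a true 20-point difference is 80% one-sided and 70% two-sided. Across the readings with a nonzero true difference it runs from 11% to 94%. These figures rest on the normal approximation with unpooled variance, on 72 analysed per group and, except in step 5, on the variance from 0.622 and 0.362.

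The stated alternative hypothesis is against the control, which is the external CBT group. A calculation for two equal groups in this trial does not power that comparison.

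**What to change.** Keep 80 per group and rewrite the paragraph:

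1. Delete the statement that ε is 0 and the wording that makes 20% a superiority margin.
2. Name P versus N as the powered comparison, with an assumed between-arm difference of 20 points.
3. Give the assumed end-of-treatment rate in each arm and the outcome threshold that defines the proportion. If the before/after rates are kept as background, say what they are.
4. Declare the sidedness and use the same one in the analysis.
5. Restate the power to match. For two-sided 5% with 72 analysed per group, this is about 69% for 56.2% vs 36.2% and about 80% for 36.2% vs 16.2%.
6. State that the calculation does not power the comparison with the external CBT group named in the alternative hypothesis.

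The cost is rewording, with no extra participants. If testing is two-sided, the stated power may fall from 80% to about 70%, depending on the arm rates chosen. Holding 80% two-sided for 20 points with the plan's variance would instead take 92 per group, or 103 with dropout; the fix does not require this.

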## Methods

### Study Design

A 3-arm superiority randomized controlled trial will be performed. The study flow is depicted in Figure 1. Patients with gadget addiction will be selected from the Kaumarbhritya Outpatient Department of MGACHRC Salod, Wardha as per inclusion criteria mentioned in Textbox 2. During the first visit, Parents will be asked whether they would like to deaddict their child from gadget addiction if they are willing then written informed assent will be obtained from the participants’ guardian. Participants will then complete questionnaires on the internet addiction test scale and digital addiction scale. Furthermore, participants’ social behavior and Prakruti (physical and mental constitution) will be assessed. As well as age, gender, socioeconomic status, and type of gadget he or she is using frequently, and the purpose of gadget use will be assessed. After this period, participants will be randomly allocated to both intervention groups in a 1:1 allocation ratio. After this, Medhya Rasayana will be prescribed to participants in group I according to age-wise doses at a frequency of twice a day for a period of 90 days as mentioned in Table 1. Participants allocated to group II will be counseled regarding the adverse effects of gadget addiction on physical and mental health and advised to follow the following routine daily for a period of 90 days, details of nonpharmacological interventions are described in Tables 1 and 2. Yoga (sun salutations, meditation), Targeted reduction in Gadget use time Padanshik krama, that is, reduce gadget use time by one-fourth part each week. Reduced time will be used for adventure, bravery, cognitive skill-oriented things, sports, and yoga. Patients will be counseled to play indoor and outdoor games daily. Encouragement toward attending social programs whenever required and feasible, encouragement of parent-child relationship by advising parents to spend a minimum of 2 hours of quality time daily with children and to give a reward for not using mobile with encouraging children to learn new things, participate in group activities with peers and teach etiquette. Initial training in sun salutation and the method of meditation will be given to participants and their parents at the time of enrollment. Children will be asked to do the proposed sun salutation and meditation on the assessment day. Participants not responding or not following instructions will be eliminated from the study. Group III will be the external group due to the fact that cognitive behavioral therapy requires trained professionals and there are time and financial constraints as well. Hence, in this published data of previously conducted clinical trials, cognitive behavioral therapy intervention in the management of gadgets or internet addiction will be used for comparison with Medhya Rasayana and Ayurveda nonpharmacological interventions. On the 30th, 60th, and 90th days of treatment, participants will be evaluated using the internet addiction test scale and the *DSM-5* (*Diagnostic and Statistical Manual of Mental Disorders, Fifth Edition*) scale for social behavior. A follow-up will be conducted on the 180th day to determine whether the intervention’s possible effects are lasting.

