### Assessment of Participants

All participants will be assessed for level of addiction, social behavior, and Prakruti (physical and mental constitution) before initiating the intervention during the study at 0, 30, 60, and 90 days, and on the follow-up day at180 days at Mahatma Gandhi Ayurved Hospital Salod (H). For the assessment of gadget addiction, an internet addiction test scale [31] questionnaire and a digital addiction scale [32] will be used. There are 20 statements on this questionnaire. After carefully reading each statement, participants have to choose the response (0, 1, 2, 3, 4, or 5) that best describes him or her using the 5-point Likert scale. Select the option that most accurately reflects how participants have been spending their time over the past month if 2 options seem to fit equally well. Along with participants, their parents or caretakers will be asked the following question regarding the gadget-addicted behavior of their children and the mean of both scores will be calculated to avoid bias in the study. The social behavior of the patient will be assessed by *DSM-5* [33] criteria on the proposed day Prakruti examination will conducted on the day of initiation of intervention by Ayusoft software [34].

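### One person both randomises and enrols, with no concealment described, so the claim that a random number table avoids selection bias is unsupported

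*Protocol article*

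**What the plan says.** The protocol article, Participants, names its safeguard: "A computer-generated random number table will be used to avoid selection bias in the study". The next sentence assigns the roles: "The principal investigator will carry out the process of randomization and enroll the participants". The article describes no separate holder of the list, no sealed envelopes, no central allocation and no masking.

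The same section says that "80 participants will be recruited after randomization in each group". Study Design gives the order step by step: parental agreement, then baseline questionnaires, and then "After this period, participants will be randomly allocated to both intervention groups in a 1:1 allocation ratio".

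The two randomised treatments differ openly. In one arm, "Medhya Rasayana will be prescribed to participants in group I according to age-wise doses at a frequency of twice a day". In the other, "Participants allocated to group II will be counseled regarding the adverse effects of gadget addiction on physical and mental health", together with yoga, meditation and a stepwise cut in gadget time. Under Assessment of Participants, child and parent both answer the addiction questionnaire and "the mean of both scores will be calculated to avoid bias in the study". Data Quality Assessment says that no committee monitors the trial data, but that progress is discussed monthly with a supervisor.

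**The concern.** Generating a sequence and concealing it are separate safeguards. The first makes the order of assignments unpredictable in principle. The second keeps it unpredictable to the person who decides whether the next family enters. The article claims the benefit of both, describes only the first, and then gives one person the two roles that concealment is meant to keep apart.

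Entry leaves room for judgement. It depends on parents' willingness, on exclusions for behavioural and systemic disorders, and on a diagnosis that the Discussion itself says may be made too readily when parents are overanxious. The nonpharmacological arm also depends heavily on parents, who are asked for at least two hours of quality time a day and for rewards. An investigator who could foresee the next assignment might, without intending it, press harder to enrol a motivated family when that arm is next.

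At stake is the comparison of Medhya Rasayana with the nonpharmacological programme. The cognitive behavioural therapy group is external published data, so this is the only contrast that randomisation protects.

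**Working it through.** **1. The roles and the claim, side by side.**

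| Question | What the article states | Where |
|---|---|---|
| What protects against selection bias? | A computer-generated random number table | Participants |
| Who runs randomisation? | The principal investigator | Participants |
| Who enrols? | The principal investigator | Participants |
| How is the next assignment hidden from the enroller? | Not described | – |
| When does allocation occur? | After consent and baseline | Study Design |

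The claim in the first row needs an answer in the fourth. The second and third rows make that answer more necessary, because the usual separation of roles is absent.

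**2. Whether later steps would repair it.** An oral preparation and a counselling and yoga programme cannot look alike to child, parent or treating staff; this is inferred from the interventions, since the article does not mention masking. The score is the mean of child and parent answers, and both know the treatment. So there is little later protection. One partial safeguard exists: the IAT is recorded on day 0, so an imbalance in baseline severity can be seen and adjusted for. Parental motivation has no such measure.

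**3. The plan's own sample size.** Inputs from Participants: P1 = 0.622, P2 = 0.362, difference 0.20, z values 1.64 and 0.84, dropout 10%. With the missing bracket in the printed formula restored:

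- variance term: 0.622 × 0.378 + 0.362 × 0.638 = 0.235116 + 0.230956 = 0.466072
- N = (1.64 + 0.84)² × 0.466072 / 0.20² = 6.1504 × 0.466072 / 0.04 = 71.66, rounded up to 72 per group
- with dropout: 72 / (1 − 0.10) = 80 per group

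Both stated figures reproduce. Changing how allocation is concealed alters neither.

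**4. Size, as an assumed range.** The documents give no figure for how far enrolment might be steered. Assume no true effect, a continuous outcome with SD 1, 72 analysed per arm, an unadjusted two-sided 5% test, and an imbalance of b SD between arms.

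- SE = √(2/72) = 0.1667
- type I error = 1 − Φ(1.96 − b/SE) + Φ(−1.96 − b/SE)

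| b (SD) | b/SE | Type I error |
|---|---|---|
| 0 | 0 | 5.0% |
| 0.1 | 0.6 | 9.2% |
| 0.2 | 1.2 | 22.4% |
| 0.3 | 1.8 | 43.7% |

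With 80 per arm the last three become 9.7%, 24.4% and 47.5%.

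**The case against.** The strongest reply is that this is a condensed article. Concealment is often left to the full protocol, which is not shown, and the sentence on roles says who carries out randomisation, not whether the list is open or how assignments are released. That stands in part: foreknowledge of the next assignment is an inference, and an unseen concealment step could lessen the problem. It does not remove the point, which rests on a stated assignment of roles set against a stated claim of protection.

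A second reply is that the analysis already sees baseline severity, through the day-0 IAT, the repeated measures ANOVA and the planned severity subgroups. This holds for severity. It does not hold for unmeasured prognosis such as parental commitment.

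Three stronger readings are tempting, and the documents do not support them:

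- A reader might infer from "80 participants will be recruited after randomization in each group" that children are randomised before consent. The phrase concludes the sample size paragraph and is most easily read as 80 per group once randomised, while Study Design gives a clear order. It is loose wording to be aligned, not evidence of the wrong sequence.
- A reader might infer that a random number table cannot deliver 80 and 80. The article never says that randomisation is simple and unrestricted. Study Design fixes a 1:1 ratio, Table 1 fixes 80 per arm, and such a table can be used to produce exactly that.
- A reader might attach one bias figure to the trial. Any such figure needs an invented degree of steering, and the sample size is based on proportions with a one-sided z of 1.64, not on a continuous two-sided test. Only a labelled range is defensible.

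**Conclusion.** The concern holds as a risk of selection bias. One person is given both randomisation and enrolment, no concealment is described, and so the statement that the random number table avoids selection bias is unsupported. The article does not show that the investigator will know the next assignment or that bias will occur, and it should not be read that way.

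The 9% to 44% range shows only that modest imbalances matter at this sample size. It rests on assumed imbalances of 0.1 to 0.3 SD, a continuous outcome, a two-sided test and no adjustment. Adjusting for baseline IAT would reduce the part that runs through severity and leave the rest.

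The point should be fixed, because the only randomised contrast in the trial depends on it and open treatments with child- and parent-rated outcomes offer little later protection.

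**What to change.** 1. Have a person who does not enrol generate and hold the list. The supervisor named under Data Quality Assessment is a candidate, provided that he or she does not recruit. The statistician is less certain, since Statistical Analysis says only that a consultation will be considered, and only for choosing methods.
2. That person supplies sequentially numbered, opaque, sealed envelopes. Each is opened only after consent, eligibility and the baseline IAT score are recorded. Varying block sizes or stratifying by severity are optional; concealment does not require them.
3. In Participants, replace the sentence on roles with this procedure, and reword the phrase that puts recruitment after randomisation so that it matches the order in Study Design.
4. The Results section says that the trial began in December 2023, so the change cannot conceal assignments already made. For those children, document how allocation was done and who could see the list, adjust the comparison for baseline IAT, and report the limitation.

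The cost is a few hours of one person's time, envelopes, a short protocol amendment and a written record of past allocations. The sample size stays at 72 per group, or 80 with dropout.
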